#### Clinical symptoms

We expect that participants who follow the MBSR training will show a larger decrease in perceived stress, anxiety, and depressive symptoms compared to wait-list control participants. To statistically test the difference in perceived stress between the MBSR and the wait-list control groups post-treatment we will use an ANCOVA, including baseline PSS scores as covariates. Thus, the dependent variable will be post-treatment PSS score and group will be used as a between subject factor with two levels (MBSR, wait-list). The primary analysis will be performed with an intention-to-treat approach and sensitivity analyses will be conducted with different scenarios of imputed datasets to examine the influence of missing data on outcomes. Additional covariates will be added to account for individual differences (university, sex, age, and recruitment wave). Similar analyses will be performed on the following secondary clinical measures: depressive and anxiety symptoms, alcohol use, stress resilience, positive mental health and daily-life stress. Perceived stress at follow-up will be assessed by a linear mixed effect regression analysis with group (MBSR, wait-list), time (baseline, post-treatment), university, sex, age, and recruitment wave as fixed factors, as well as a group x time interaction. The intercept will be allowed to vary across participants to account for between-subject variability. Other clinical assessments, such as those assessing repetitive negative thinking, cognitive reactivity, allowing of emotions, mindfulness skills, self-compassion will be tested as potential mediating factors to determine whether changes in those scores after treatment can explain changes in the primary outcome at follow-up (i.e., PSS score). Mediation analyses will be conducted on the per-protocol sample (i.e., those participants who attended 50% or more of the training). Clinical assessments such as those assessing childhood trauma and personality traits at baseline will be tested as potential moderators of the clinical outcome.

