**Methods:**

This study is a longitudinal two-arm randomised, wait-list controlled trial to investigate the effects of MBSR on a preselected, Dutch university student population with elevated stress levels. Clinical symptoms are measured at baseline, post-treatment, and three months after training. Our primary clinical symptom is perceived stress, with additional measures of depressive and anxiety symptoms, alcohol use, stress resilience, positive mental health, and stress reactivity in daily life. We investigate the effects of MBSR on stress regulation in terms of behaviour, self-report measures, physiology, and brain activity. Repetitive negative thinking, cognitive reactivity, emotional allowance, mindfulness skills, and self-compassion will be tested as potential mediating factors for the clinical effects of MBSR. Childhood trauma, personality traits and baseline brain activity patterns will be tested as potential moderators of the clinical outcomes.

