Thus, the goals of the current study are to (1) establish clinical effects of MBSR in a population of Dutch university students with high levels of perceived stress, (2) identify the effect of MBSR on stress regulation, (3) assess the role of large-scale networks in this process, and (4) identify for whom MBSR might be more beneficial. Our main hypothesis regarding aim (1) is that MBSR is effective at reducing self-reported perceived stress in a population of highly stressed university students, sustained over a 3-month follow-up period. We expect to replicate previous studies showing the efficacy of MBSR within student populations [30–33] and we expect that MBSR is also effective at reducing other relevant clinical symptoms in this population, such as depression and anxiety symptoms [9]. Regarding aims (2) and (3) (i.e., the effects of MBSR on stress regulation and the role of large-scale networks in this process), we hypothesise that MBSR leads specifically to concurrent enhancement of cognitive control *and* affective processing across the different domains of stress-regulation described above. Moreover, we expect that these measures at baseline will be important in predicting individual differences in effectiveness of MBSR, and that changes in these measures will be accompanied by changes at the clinical level for aim (4).

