## Methods

### Design

This study is a two-arm randomised, wait-list controlled trial with ethical approval from the local medical-ethical committee (METC Oost-Nederland), see Fig. 1. Participants are randomised into a treatment and a wait-list control group after baseline measurements including clinical, neurocognitive, and ecological momentary assessments. In the following two months, the treatment group participates in an MBSR training, and the wait-list group receives no planned intervention for two months, serving the purpose of assessing the effect of the intervention on the study outcomes against not receiving treatment during the same time-period. Post-treatment measurements take place three months after baseline, and they include another set of clinical, neurocognitive, and ecological momentary assessments. Six months after baseline there is a follow-up clinical assessment. After this assessment, the participants in the wait-list group receive the MBSR training, after which they complete a final clinical assessment.

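### The model for perceived stress at follow-up lists no follow-up level of time, so as specified it does not test the sustained effect

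*Protocol article*

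**What the plan says.** The Background section gives the main hypothesis for aim 1: "MBSR is effective at reducing self-reported perceived stress in a population of highly stressed university students, sustained over a 3-month follow-up period". Persistence is therefore part of the hypothesis itself.

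The article treats follow-up as its own occasion. The abstract lists three: "Clinical symptoms are measured at baseline, post-treatment, and three months after training". The Design section places the post-treatment measurements three months after baseline, and then adds: "Six months after baseline there is a follow-up clinical assessment". Wait-list participants are trained only after that assessment, so both randomised groups are still comparable when it takes place.

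The Clinical symptoms section describes two analyses of PSS by group. The primary one is an ANCOVA with baseline PSS as covariate: "Thus, the dependent variable will be post-treatment PSS score". The second is introduced as the follow-up analysis: "Perceived stress at follow-up will be assessed by a linear mixed effect regression analysis with group (MBSR, wait-list), time (baseline, post-treatment". The bracket ends there. University, sex, age and recruitment wave are further fixed factors, and the sentence closes with the interaction and the random effect: "as well as a group x time interaction. The intercept will be allowed to vary across participants".

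**The concern.** The subject of the sentence and the model in it do not match. The sentence announces an analysis of PSS at follow-up, but the time factor it defines contains only the two earlier visits. An analyst who follows the text would leave the follow-up visit out and obtain a second estimate of the post-treatment effect.

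What is at stake is the persistence part of the main hypothesis. The data for a randomised comparison at follow-up are to be collected, but the analysis named for them does not use them. The correction is also not unique. One could add a third level, put follow-up in place of post-treatment, or model the later visits with baseline PSS as a covariate. These are different models with different contrasts, so the choice should be fixed in writing before the data are seen.

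**Working it through.** No figure in the plan bears on this point, so there is none to reproduce. The check is whether the specified model contains a parameter for follow-up, and whether another analysis supplies one.

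**1. Can post-treatment be read as including follow-up?** No. The abstract, the Design section and the Follow-up part of Procedures (visit 5) all separate the two. They describe the timing of follow-up differently (three months after training, six months after baseline, two months after the post-intervention visits), but each places it after the post-treatment visit.

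**2. What does the specified model estimate?** Let G = 1 for MBSR and 0 for wait-list, and P = 1 at post-treatment and 0 at baseline. Leaving out the covariates and the random intercept, the mean PSS is

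b0 + b1·G + b2·P + b3·G·P.

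- Mean change in MBSR, baseline to post-treatment: b2 + b3.
- Mean change in wait-list: b2.
- Difference: b3.

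The group-by-time interaction is b3, the post-treatment effect. A follow-up record has no value on this time factor and cannot enter the model.

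**3. What changes with a third level?** Let F = 1 at follow-up. Two terms are added: b4·F + b5·G·F. The coefficient b5 is the between-group difference in change from baseline to follow-up. Randomisation takes place after the baseline measurements, so the groups have equal expected baseline means. In expectation b5 is therefore the group difference in PSS at follow-up, which is what the persistence hypothesis needs.

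**4. Numerical illustration.** Data were simulated for 20,000 participants at three visits, with between-person variance 0.7 and residual variance 0.3. The SD is then 1 and the correlation between any two visits is 0.7. The article gives 0.7 for baseline to end of treatment only; using it for the other pairs is an assumption. The true effect was set to -0.4 at post-treatment and 0 at follow-up, that is, an effect that does not last.

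| Levels of time | Group × post-treatment | Group × follow-up |
|---|---|---|
| baseline, post-treatment | -0.394 | no coefficient |
| baseline, post-treatment, follow-up | -0.394 | 0.001 |

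The two-level model recovers the post-treatment effect and says nothing about whether it has faded. The three-level model shows that it has.

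**5. Does another analysis fill the gap?**

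- The primary ANCOVA has post-treatment PSS as its outcome.
- The similar analyses promised for secondary measures concern depressive and anxiety symptoms, alcohol use, resilience, positive mental health and daily-life stress, not PSS at follow-up.
- The mediation analysis does refer to PSS at follow-up. It is restricted to participants who attended at least half of the training, and it asks whether changes in mediators explain change in PSS. It is not a comparison of the groups as randomised.

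**The case against.** The best reply is that this is a slip. The sentence states its purpose, the follow-up data are collected in both groups before the wait-list group is trained, and the same pair of levels appears in the MRI, fear-conditioning and emotional-conflict models. There it is correct, because those measures are taken at two visits only. A bracket carried over from those models is the likeliest explanation. This stands, and it limits the point: the error lies in the specification, not in the stated intent. It does not remove the point. A condensed article may leave levels out, but this one states them, and they contradict the purpose of the sentence.

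Three stronger readings are tempting, and the documents support none of them.

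- A reader might infer that the trial will never test persistence. The text commits to assessing follow-up PSS, so the supportable statement is that the model as written does not do so.
- A reader might infer that a post-treatment result will be reported as a follow-up result. That is a prediction about conduct, and the article does not say it.
- A reader might attach an efficiency loss. With free baseline means, the change contrast has variance 2/(1 + r) relative to ANCOVA, which at r = 0.7 is 2/1.7 = 1.18, or about 15% of participants (1 - 1/1.18). That concerns change scores versus ANCOVA, not a missing visit. It assumes equal SDs, the 0.7 is a baseline to end-of-treatment value, and no baseline-to-follow-up correlation is given. The ANCOVA remains primary, so no primary power is lost.

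Nor is the random intercept ("The intercept will be allowed to vary across participants to account for between-subject variability") an error in the model as stated. Its implication of equal correlation between all pairs of visits becomes a question only once a third visit is included.

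**Conclusion.** The point holds for the analysis as specified. The model named for follow-up PSS has one group-by-time parameter, for post-treatment, and none for follow-up. The part of the main hypothesis that reads "sustained over a 3-month follow-up period" therefore has no specified test in the article, although the intent to assess it is plain.

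The extent is all or nothing rather than a percentage: follow-up PSS contributes no observations to this model. The primary ANCOVA, its power and the target sample size all concern post-treatment PSS and are untouched. The conclusion rests on reading the bracketed levels as complete, and on the article alone. A separate analysis plan might list three levels, but the contradiction printed here would still need correcting.

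**What to change.** In the Clinical symptoms section, list the levels of time as baseline, post-treatment and follow-up. Name the group difference in PSS at follow-up (the group-by-time contrast at that visit, by intention to treat) as the test of the sustained effect. Tie the follow-up level to visit 5, and reconcile the differing descriptions of its timing.

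Two refinements are optional and not part of the error. The model could adjust for baseline PSS, as the primary ANCOVA does, and it could allow a less restrictive covariance across the three visits than a random intercept gives. The ways of handling baseline are not interchangeable in every detail, so the plan should say which is used.

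The cost is one sentence of analysis wording. It needs no new data, no extra visits and no change to the sample size.

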### Statistical analysis

#### Sample size calculation

The sample size, which is reported on http://trialregister.gov, was calculated on the basis of our planned Analysis of Covariance (ANCOVA) to estimate the difference between groups in perceived stress at post-treatment, while taking into account individual baseline measurements of perceived stress as a covariate. We use the method of Borm, Fransen, & Lemmens (2007), which adjusts the sample size calculated for an independent sample t-test by multiplying with the factor (1-r^2), where r is the correlation coefficient between baseline and post-treatment measurement. We aim to achieve a power of 80% with an *α* = 0.05. The correlation between baseline and end-of-treatment perceived stress is estimated at *r* = 0.7, based on data from Verweij et al. (2018). Assuming a moderate effect size of Cohen's *d* = 0.4, as reported by a large RCT on a general student sample (Galante et al., 2018), we would need 54 participants per group. Taking also into account an average attrition rate (10%) of studies on student populations reported in a meta-analysis by Khoury et al. (2015), we aim to recruit a total of 60 participants per group.

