#### MRI analysis

Neuroimaging data from all tasks will be analysed using various neuroimaging software packages, including FSL, SPM, (Turbo-) Brainvoyager, Nipype, as well as custom analysis scripts. The data will be first pre-processed, to remove artefacts, such as movement and physiological noise. General Linear Models will then be used per participant, per task, with regressors representing task activity, as well as nuisance parameters such as motion parameters and physiological noise parameters. Parameter estimates will then be introduced into second level a mixed-effect model with group (MBSR, wait-list), and time (baseline, post-treatment) as fixed factors, as well as a group x time interaction. Additional fixed factors will be added (university, sex, age, and recruitment wave). A random intercept for participants will be included to account for individual differences. In all tasks we will assess brain connectivity patterns of three large-scale brain networks (SN, ECN, DMN). Connectivity will be operationalised as the correlation coefficients between activity time-courses of nodes of these networks. Within- and between-network connectivity will be calculated to determine network cohesion and between-network communication, respectively. Potential connectivity patterns we observe (e.g., changes in SN or ECN within-network connectivity) will be tested as potential moderators of the clinical outcome post-treatment.

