#### Implicit, exogenous stress-regulation – fear conditioning and extinction task

Based on current fear learning and extinction literature we hypothesise that MBSR will enhance CS differentiation because of clinically promoted awareness to bodily signals and negative affect. We expect this heightened awareness during contextual extinction to lead to better extinction retention at day 2 without affecting fear renewal. Therefore, we expect less spontaneous recovery of the fearful memory when being exposed to the extinguished CS + compared to the CS-. At the physiological level this means that smaller pupil diameter and skin conductance response differences between CS + and CS- are expected in the MBSR group in the early stages of extinction retention compared to the wait-list control group. Similarly, for our self-report measurements, we expect to observe lower perceived fear ratings in the MBSR group in the early stages of extinction retention, differentiating the CS + and CS- compared to the wait-list control group. In our brain imaging measures, we expect that MBSR induces increased connectivity within SN during the extinction phase. We will statistically test differences in outcome physiological measures (skin conductance and pupillometry) between groups with mixed-effect regression analysis on each of the phases of the paradigm (conditioning, extinction, extinction retention, fear renewal). Fixed effects will include stimulus type (CS + , CS-), group (MBSR, wait-list), and time (baseline, post-treatment), as well as a group x stimulus type x time interaction. Additional fixed factors will be added (university, sex, age, and recruitment wave) and a random intercept for participants will be included to account for individual differences. Our main outcome in this task is extinction memory retention a day after extinction learning. Therefore, we will focus on the interaction effect of group x stimulus type x time during the extinction retention phase.

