#### Explicit, exogenous stress-regulation – emotional stroop task

We expect that MBSR will affect participants’ responses when they are asked to identify and respond to emotionally conflicting information. In terms of behaviour, we expect to observe this as a reduction in response time in incongruent emotional situations. On our brain imaging measurements, we expect that MBSR will enhance ECN and SN within-network connectivity during emotional conflict processing. We will statistically test differences in behavioural outcome measures (reaction time and accuracy) between groups with linear mixed-effect regression analysis. Fixed factors will include group (MBSR, wait-list), time (baseline, post-treatment), congruency (congruent, incongruent), as well as a group x congruency x time interaction. Additional fixed factors will be added (university, sex, age, and recruitment wave) and a random intercept for participants will be included to account for individual differences.

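### The follow-up PSS and MRI models test group x time with a free group difference at baseline, which is valid but less precise than the baseline adjustment used for the primary outcome

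*Protocol article*

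**What the plan says.** All references are to the Statistical analysis part of the protocol article unless stated otherwise.

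- **Sample size calculation.** The size is set for the post-treatment PSS comparison by ANCOVA. The t-test size is reduced by "multiplying with the factor (1-r^2), where r is the correlation coefficient between baseline and post-treatment measurement", with r = 0.7. The targets are "We aim to achieve a power of 80% with an *α* = 0.05" and "Assuming a moderate effect size of Cohen's *d* = 0.4", giving 54 per group, or 60 with 10% attrition.
- **Clinical symptoms.** Post-treatment PSS is tested by that ANCOVA, and the secondary clinical measures are to be analysed similarly. PSS at follow-up goes to a mixed model with a random participant intercept, a group factor and "time (baseline, post-treatment), university, sex, age, and recruitment wave as fixed factors, as well as a group x time interaction". It has no baseline covariate and no constraint that the arms start equal.
- **MRI analysis.** The parameter estimates enter a "mixed-effect model with group (MBSR, wait-list), and time (baseline, post-treatment) as fixed factors, as well as a group x time interaction", again with a random intercept. The resting-state analysis takes over this model and adds a factor for before and after stress induction.
- **Fear task.** For the main outcome, "we will focus on the interaction effect of group x stimulus type x time during the extinction retention phase".
- **Emotional Stroop task.** The model has group, time and congruency, "as well as a group x congruency x time interaction".
- **Neurofeedback task.** The model has no time term. The task is added only at the post-intervention visits.
- **Randomisation** (Methods). Allocation is made after all baseline assessments.

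**The concern.** The protocol uses two ways of handling baseline. In the ANCOVA, baseline is a covariate. In the mixed models, baseline is an outcome at one level of time, each arm has its own baseline mean, and the treatment effect is the difference between arms in change.

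Since allocation follows baseline, the arms differ there only by chance. Estimating a separate baseline difference and subtracting it in full adds noise, whereas ANCOVA subtracts only the part that the baseline-to-later correlation supports. For the same reason, a chance baseline imbalance passes through regression to the mean into the group x time estimate, which can then differ from the ANCOVA result on the same scale.

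At stake is the precision of the sustained-effect part of the main hypothesis and of the network outcomes. The sample size section expects the task outcomes to be well powered on the strength of the clinical sizing, and the Update section repeats this while expecting recruitment to fall short. Precision that can be had from data already collected is therefore worth keeping.

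**Working it through.** **Inputs.** From the sample size section: power 80%, alpha 0.05 (two-sided assumed, since sidedness is not stated), d = 0.4, r = 0.7 between baseline and end of treatment, 54 evaluable per group. The same section quotes d = 0.28–0.92 for connectivity and 0.93–1.15 for extinction retention. The protocol gives no correlation for follow-up PSS, MRI or task outcomes, so other values of r below are assumptions.

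**1. The plan's own figure.** A two-sided t-test at d = 0.4 needs 99 per group (normal approximation) or 100 (t distribution). The ANCOVA factor is 1 − 0.7² = 0.51, so 99 × 0.51 = 50.5 and 100 × 0.51 = 51. With a t critical value and 2n − 3 degrees of freedom, the ANCOVA needs 52. The stated 54 lies slightly above this, and 54/0.9 = 60. The primary sizing stands.

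**2. What group x time estimates.** With two visits, complete data, a random intercept and a free group effect, the interaction is the difference between arms in mean change. In a simulated complete data set the mixed model gave −0.3073 (SE 0.1385), the change-score comparison gave −0.3073 (SE 0.1385), and the ANCOVA standard error was 0.1338.

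**3. Variance factors** (equal SDs at both visits, relative to a comparison of later values alone = 1):

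- Group x time: 2(1 − r). At r = 0.7 this is 0.60.
- Baseline-adjusted: 1 − r². At r = 0.7 this is 0.51.
- Ratio: (1 − r²)/[2(1 − r)] = (1 + r)/2. At r = 0.7 this is 0.85.

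At r = 0.7, group x time keeps 40 of the 49 points of variance reduction that ANCOVA obtains.

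**4. Power.** Two-sided t, 54 per group. The standardised effect is d/√[2(1 − r)] with 2n − 2 degrees of freedom for group x time, and d/√(1 − r²) with 2n − 3 for baseline adjustment.

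| d | r | Group x time | Baseline-adjusted |
|---|---|---|---|
| 0.4 | 0.7 (plan) | 75.8% | 82.2% |
| 0.4 | 0.6 (assumed) | 63.4% | 73.0% |
| 0.4 | 0.5 (assumed) | 54.0% | 66.2% |
| 0.28 | 0.7 (assumed for MRI) | 46.1% | 52.3% |
| 0.28 | 0.3 (assumed) | 23.0% | 32.7% |

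A simulation of 4,000 trials at d = 0.4 and r = 0.7 gave 75.7% for the change score and 81.5% for ANCOVA.

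**5. Size needed for 80% at d = 0.4, r = 0.7.** Group x time needs 60 evaluable per group (60/0.9 = 66.7, so 67 recruited). Baseline adjustment needs 52 (52/0.9 = 57.8, so 58 recruited). The plan provides 54.

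**6. Reach of these figures.** They apply to one value per participant per visit: follow-up PSS once a later visit is in the model, and connectivity outcomes with two time levels. The fear and Stroop tests also estimate a change, in the CS+/CS− or congruency contrast. However, those models have four cells per person and only a random intercept, so their standard error is not the change-score one. In one simulation of such a design (residual SD 1, person-level contrast SD 2) the model's standard error was 0.59 against an empirical SD of 0.39. The power figures above therefore do not carry over to those tests. The same caution applies to the resting-state terms that involve the before/after stress factor.

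**The case against.** The strongest reply is that this is a choice of efficiency and not an error. Group x time is valid and unbiased under randomisation, it speaks directly to the hypothesis of a larger decrease, and a mixed model can keep participants with a missing visit. All of that is true. It does not favour the free-baseline form, however. A mixed model with a common baseline mean keeps the same participants, and baseline adjustment tests the same hypothesis with a smaller variance.

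The limits on scope also stand. A reader might infer that the sample size is undermined because it was built on the (1 − r²) reduction. The documents do not support that: the sizing is for post-treatment PSS, which is analysed by the matching ANCOVA, and the secondary clinical measures are treated similarly. Nor is the gain from baseline lost at r = 0.7, since most of it remains.

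A reader might also infer that the tests are worse than ignoring baseline. That needs r below 0.5, and nothing in the protocol supports or excludes such a value.

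For extinction retention, the main fear-task outcome, the protocol cites d = 0.93–1.15. In a simple two-visit comparison at d = 0.93, power would be 98.2% against 99.9% at an assumed r = 0.3, a difference under 2 points. Neurofeedback has no baseline measurement and is outside the point.

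Finally, the follow-up sentence has a more basic fault: its time levels omit the follow-up visit. Adding that visit is necessary but would leave the free baseline difference in place.

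**Conclusion.** The point holds as an avoidable loss of precision in the follow-up PSS model and the two-level MRI/connectivity models. The fear and Stroop tests share the change-from-baseline structure, but no power figure is attached to them here.

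At the plan's d = 0.4 and r = 0.7 with 54 per group, power is about 76% instead of 82%, and 60 instead of 52 evaluable participants per group are needed for 80%. For follow-up this assumes that r = 0.7, which the protocol gives for baseline to end of treatment, also holds at the later visit. It further assumes complete data and equal SDs at the two visits. The larger losses, such as 23% against 33% at d = 0.28 and r = 0.3, illustrate assumed correlations and are not findings about this trial. At d of about 0.9 the loss is negligible.

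The primary ANCOVA, the similarly analysed secondary clinical outcomes, the 54/60 per group and the neurofeedback model are unaffected. The point is no ground for calling any of the tests biased or invalid.

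**What to change.** - **Follow-up PSS.** Include the follow-up visit in the model. Then either take the post-baseline PSS values as outcome, with baseline PSS as covariate and a group x visit term, and read the group effect at follow-up; or keep the mixed model with baseline as a time level and give both arms a common baseline mean.
- **MRI/connectivity outcomes with two time levels.** Use the same baseline-adjusted or common-baseline form.
- **Fear and Stroop tasks.** Compare the arms on the post-treatment condition contrast (CS+ minus CS−, incongruent minus congruent), with the participant's own baseline contrast as covariate.
- **Power statements.** Do not apply the two-visit power figures to the three-way task models.

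The other planned covariates can stay. The change costs only analysis wording, with no new data, visits or participants. The common-baseline assumption is justified because allocation follows baseline.

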### Randomisation

Groups of maximally 20 participants at a time (because of limitations in scanning capacity) are recruited and are randomly assigned to either the MBSR or waitlist control condition. This ensures that equal numbers of experimental and control group participants are recruited at any given time-period. Randomisation is conducted after baseline clinical, neurocognitive, and ecological momentary assessments. The procedure is carried out by an automated custom Python script using computer-generated random numbers, taking into account stratification for gender and University (i.e., Radboud University, or Hogeschool Arnhem Nijmegen). Baseline measurements occur before group assignments and therefore both participants and researchers are blinded to these measurements. Post-treatment measurements are not blinded.

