#### Intervention

Participants in the MBSR group receive the MBSR training and their attendance is logged, while participants in the wait-list group will not receive any planned intervention or measurements for the corresponding 8 weeks.

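### Mediation is planned only in participants who attended at least half the training, so the treatment-to-mediator path is no longer a randomised comparison

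*Protocol article*

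**What the plan says.** The Clinical symptoms part of the statistical analysis section names one analysis set for mediation: "Mediation analyses will be conducted on the per-protocol sample (i.e., those participants who attended 50% or more of the training". The question put to that set is whether "changes in those scores after treatment can explain changes in the primary outcome at follow-up". The mediators are thus the post-treatment changes in repetitive negative thinking, cognitive reactivity, allowing of emotions, mindfulness skills and self-compassion, and the outcome is PSS at follow-up.

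The same section says of the main comparison: "The primary analysis will be performed with an intention-to-treat approach". That statement covers the primary analysis. No mediation analysis in the full randomised sample is described, and the article does not say how the attendance rule applies to the wait-list arm.

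Four statements elsewhere fix the timing:

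- Randomisation: "Randomisation is conducted after baseline clinical, neurocognitive, and ecological momentary assessments".
- Procedures, Intervention, on the trained arm: "Participants in the MBSR group receive the MBSR training and their attendance is logged".
- Procedures, Intervention, on the other arm: "participants in the wait-list group will not receive any planned intervention or measurements for the corresponding 8 weeks".
- Design, on what happens after the six-month assessment: "After this assessment, the participants in the wait-list group receive the MBSR training".

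**The concern.** A mediation analysis in a randomised trial has two links. The link from mediator to outcome is observational whatever sample is used. The link from allocation to mediator is the one that randomisation protects, and it keeps that protection only if the groups compared are those that were randomised.

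Selecting on attendance gives it up. People who complete at least half of a demanding eight-week course may differ from those who do not in motivation, stress or rumination, and these may also bear on the mediators and on later PSS. If the selection acts in one arm only, a difference in mediators between the arms can appear without any effect of MBSR. The total effect on follow-up PSS, which the mediation analysis is meant to split, is exposed to the same selection.

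At stake is how far the trial's account of the psychological route by which MBSR works can be read causally.

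**Working it through.** **1. Can a wait-list participant satisfy the rule in time?** In order, the design runs: baseline; randomisation; eight weeks of MBSR in one arm while "the wait-list group receives no planned intervention for two months"; post-treatment assessment (mediators); follow-up assessment (PSS); then MBSR for the wait-list arm. Training attended by wait-list participants comes after both mediator and outcome have been recorded. Within the period analysed, no wait-list participant has any attendance.

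**2. What do the two readings leave?**

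- Literal: only MBSR attenders remain. There is no comparison between arms, only an uncontrolled association of pre-post changes.
- Charitable: MBSR attenders are compared with the whole wait-list arm. A contrast remains, but one side has been selected after randomisation.

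Neither is the randomised comparison.

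**3. The plan's own figure.** The article gives no number for the mediation analysis. Its only sample size is for the primary ANCOVA: d = 0.4, r = 0.7, α = 0.05 (two-sided assumed), power 80%. The normal approximation gives 2 × (1.960 + 0.842)² / 0.4² = 98.1 per group; multiplied by 1 − 0.7² = 0.51 this is 50.0, or 51 when rounded up at each step. A noncentral t calculation on the adjusted variance gives 52. The stated 54 is slightly conservative, and 54 / 0.9 = 60 matches the recruitment target. These figures do not bear on the choice of analysis set; 54 is used below only as the arm size.

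**4. How large could the selection effect be under the charitable reading?** The documents give neither the attendance rate nor its relation to the mediators, so both are assumed. Let a share q of the MBSR arm attend enough, these being the top fraction q of a latent normal trait that has correlation ρ with the baseline-adjusted mediator. Let MBSR have no true effect on the mediator. Then, with c the (1 − q) quantile of the standard normal and φ its density:

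- mean of the trait among attenders: m = φ(c) / q
- false difference in the mediator: b = ρ × m, in SD
- variance among attenders: v = 1 − ρ² × m × (m − c)
- standard error: √(v / (54q) + 1 / 54)

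Worked case, q = 0.80 and ρ = 0.3: c = −0.842, φ(c) = 0.280, m = 0.280 / 0.80 = 0.350, b = 0.3 × 0.350 = 0.105 SD. Then v = 1 − 0.09 × 0.350 × 1.192 = 0.962, the standard error is √(0.962 / 43.2 + 1 / 54) = 0.202, and b / SE = 0.52. A nominal 5% two-sided test then rejects in about 8.1% of trials.

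| Attending (q) | ρ = 0.1 | ρ = 0.3 | ρ = 0.5 |
|---|---|---|---|
| 0.95 | 0.01 SD (5.0%) | 0.03 SD (5.3%) | 0.05 SD (5.9%) |
| 0.90 | 0.02 SD (5.1%) | 0.06 SD (6.0%) | 0.10 SD (7.9%) |
| 0.80 | 0.04 SD (5.3%) | 0.11 SD (8.1%) | 0.18 SD (14.3%) |
| 0.70 | 0.05 SD (5.6%) | 0.15 SD (11.0%) | 0.25 SD (23.0%) |

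In brackets: false-positive rate of the treatment-to-mediator test. The sign follows from letting attenders score better; if low attenders would have scored better, it reverses.

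**The case against.** Asking how training works among those who received enough of it is a recognised question. The plan declares it in advance and keeps it apart from the intention-to-treat primary analysis. An attendance rule in a wait-list trial is ordinarily applied only to the arm offered training, attendance is logged for that arm, and a condensed article may leave the control-arm definition to the full protocol. Much of this stands: the charitable reading is probably the intended one, and the attender question is worth keeping. But filtering one arm does not answer that question causally, and the text makes it the only mediation analysis.

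The size can also be challenged. Analysing changes removes part of any stable difference between people. Some low attenders may already be among the planned 10% attrition. With 10% non-attendance and correlations of 0.1–0.3, the illustration gives only 0.02–0.06 SD. All of this stands.

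Some stronger inferences are tempting but not supported:

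- That the bias favours MBSR. This depends on why sessions are missed, which the article does not say.
- That the upper figure of 0.25 SD can be set against the planned d = 0.4. That effect size concerns post-treatment PSS, not a mediator or follow-up PSS.
- That the attendance rule is what stops the mediation results from explaining the primary effect. The primary outcome is PSS at post-treatment and the mediation outcome is PSS at follow-up, so a mediation analysis of everyone randomised would not decompose the primary effect either.
- That wait-list participants can never meet the rule. They are trained later; the point holds up to the follow-up assessment.

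**Conclusion.** The concern holds for the secondary mediation analyses. On either reading of the attendance rule, the treatment-to-mediator path and the total effect at follow-up are not randomised comparisons. This follows from the design's own timing and needs no assumption.

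The amount of bias does need assumptions. The range of about 0.02–0.25 SD rests on 10–30% non-attendance and correlations of 0.1–0.5, none of which the article states. It applies to the charitable reading only, and its direction is unknown. At 95% attendance the same model gives at most about 0.05 SD.

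A reader might infer that the trial's main result or its central aims are undermined. They are not. The primary ANCOVA is by intention to treat, and the stress-regulation and network aims are tested through the task and imaging models, for which no attendance restriction is stated. This is a cheap improvement to a secondary analysis, to be made before the data are analysed.

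**What to change.** Make the main mediation analysis one of all randomised participants in their allocated arms. Use the post-treatment mediator and follow-up PSS, adjust for baseline mediator, baseline PSS and the stratification factors (gender and university), and handle missing data as for the primary analysis.

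Keep the analysis of those attending at least 50% as a labelled sensitivity analysis. State that it retains every wait-list participant and is not a randomised comparison.

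The cost is a change of wording. Both arms already complete the questionnaires at baseline, post-treatment and follow-up, so no new data are needed. Low attenders will dilute the estimated indirect effect slightly. The mediator-to-outcome path remains observational, and the report should say so.
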